#### Participant timeline

The schedule of enrolment, interventions, and visits for participants is shown in Figs 1 and 2.

**Fig 2 pone.0295998.g002:**
[figure not shown]
Schedule of enrolment, interventions, and assessments. *, Must be performed prior to initiation of the *Bifidobacterium bifidum* G9-1. ALT, alanine aminotransferase; AST, aspartate transaminase; BBG9-1, *Bifidobacterium bifidum* G9-1; GSRS, Gastrointestinal Symptom Rating Scale.

#### Sample size

In a sub-analysis of a previous study [15,18], BBG9-1 oral administration changed the total GSRS score by -0.441 ± 0.499. In the non-treatment period, the change in the total GSRS score was -0.197 ± 0.314. Based on these findings, assuming a difference of 0.244 ± 0.412 in the change in GSRS between the two groups in the study, we obtained an alpha error of 0.05, a power of 0.80, and a sample size ratio of 1:1; 45 cases per group would be needed to detect a significant between-group difference. Dropouts with a dropout rate of 10%, 50 cases in one group, and 100 cases in both groups have been set as the target number of cases for this study.

#### Recruitment

Outpatients with T2DM at the Department of Endocrinology and Diabetes of Kyoto Prefectural University of Medicine Hospital (Kyoto, Japan), Department of Diabetes of Kameoka Municipal Hospital (Kameoka, Japan), and Department of Diabetes and Endocrinology of Matsushita Memorial Hospital (Moriguchi, Japan) will be recruited to participate in this study.

### Assignment of interventions: Allocation

#### Sequence generation

The investigators or researchers will enter the necessary information into the web system; if eligible, based on the GSRS score and the Bristol scale score, perform the main enrolment/assignment, and confirm the results. The participants will be assigned to group A or group B using the minimization method, with age, sex, and type of symptom (constipation or diarrhea) as allocation factors.

#### Implementation

The researchers will enter the necessary information into the web system and will check the allocation.

### Data collection and management

#### Plans for assessment and collection of outcomes

The researchers will manage the data of the participants using the central registry number assigned by the data center. In this study, data on study participants reported by the researchers will be collected at each observation point using a case report form (CRF), survey forms (GSRS, BDHQ, and DTSQ), logbooks (defecation frequency, stool characteristics (Bristol scale score), and adherence to BBG9-1). We will use the average of the 1-week Bristol scale scores as the Bristol scale score. The survey forms of 12-week after the baseline examination and logbooks during the observation periods will be sealed using a special envelope and sent to the data center in such a way that the investigators or researchers cannot confirm the contents of the responses. The investigators or researchers will ensure that the survey forms and logbooks other than those answered and recorded by the research participants themselves are complete in order to ensure that the data recorded by the research participants (CRFs) are not lost or destroyed. If any data correction is necessary, the date and reason for the correction shall be recorded. Researchers shall confirm that all data, including the corrected data, are accurate and complete and shall ensure the quality of the data. For data submitted in the CRF, the data management staff will maintain a central registry of all data from the site.

#### Data management

The data management for this study will be conducted in accordance with the procedures and checklists. The study participants will be identified using their central registry numbers. The electronic transfer of data to the research participants must be approved by the data manager. When data are transferred over an unsecured electronic network, they must be encrypted at source. For the discontinued cases, data will be collected up to the point of discontinuation.

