#### Criteria for discontinuing or modifying allocated interventions

The criteria for discontinuation of observation are as follows: (1) failure to register; (2) worse glycemic control (HbA1c ≥ 10%); (3) withdrawal of consent; (4) serious incompatibility after registration; (5) discontinuation of medications because of worsening of disease and/or complications; (6) discontinuation of the trial because of illness or adverse events; (7) pregnancy; (8) significant nonadherence (< 75% of the number of tablets each participant plans to take internally or > 120%); (9) significant deviation from the research protocol; (10) investigator/researcher’s determination to stop the study for other reasons. The data shall be fixed by the Data Handling Committee after handling in a blinded manner. Even if there is a deviation from the research protocol, observations shall be continued as much as possible.

The criteria for discontinuation of the trial are as follows: (1) significant information regarding the quality, safety, or efficacy of Biofermin® tablets is obtained; (2) recruitment of research participants is difficult, and there is a large discrepancy from the planned number of cases; (3) the objective of the research is achieved before the planned number of cases or planned duration is reached; (4) instructions to change the research plan, and it is difficult to accept these instructions.

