#### Outcomes

The primary endpoint of this trial will be the change in the total GSRS score from baseline to follow-up examination (12 ± 3 weeks after baseline examination). Secondary endpoints of this trial will be as follows: (1) change and percent change in following parameters from baseline to follow-up examination: GSRS subdomain scores, fecal properties/Bristol stool form scale, defecation frequency, blood test biomarkers (total bile acid, glycoalbumin, glucagon-like peptide-1, glucose-dependent insulinotropic polypeptide, glucagon, HbA1c, fasting plasma glucose, C-peptide, AST, ALT, gamma-glutamyltransferase, total cholesterol, high-density lipoprotein cholesterol, low-density lipoprotein cholesterol, triglycerides, blood urea nitrogen, and creatinine), physical examination (body weight and body mass index), urinary albumin creatinine ratio, gut microbiota (type of enterobacteria, relative abundance, alpha diversity, and beta diversity), macronutrients (total energy, carbohydrate, fat, protein, and dietary fiber intakes measured by brief-type self-administered diet history questionnaire [BDHQ]) [16]; (2) proportion of participants whose fecal property of Bristol stool form scale is within normal range (3.5–4.5); (3) medication adherence to the BBG9-1; (4) factors that affect GSRS total score or constipation/diarrhea subdomain scores; (5) stratification of following items by baseline symptoms (constipation/diarrhea): GSRS total score, GSRS subdomain scores, proportion of participants whose fecal properties are within normal range, defecation frequency, blood test biomarkers, and gut microbiota. The exploratory endpoints of this trial will be as follows: (1) blood, urine, and stool metabolomes (short, medium, and long chain fatty acids, amino acids, carbohydrates, and bile acids); (2) items other than nutrients evaluated in the secondary endpoints and items evaluated by the diabetes treatment satisfaction questionnaire (DTSQ) [17]; (3) items other than physical examination evaluated in the secondary endpoints; (4) items other than gut microbiota evaluated in the secondary endpoints; (5) change in lipopolysaccharide-binding protein; (6) subgroup analysis by age, sex, etc. Harm outcomes will also be evaluated based on various laboratory abnormalities and adverse reactions to the medication.

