### Statistical methods

#### Statistical methods for primary and secondary outcomes

Full analysis set (FAS) analysis will be performed for the primary and secondary endpoints. If necessary, per protocol set (PPS) analysis will be performed as a sensitivity analysis for the FAS analysis. In principle, the analysis should be performed at a two-sided significance level of 5%. The person responsible for the statistical analysis will prepare a separate statistical analysis plan that specifies the details of the statistical methods, including data handling. A statistical analysis plan will be prepared before the data are fixed. The primary endpoints will be treated as validation results, whereas the other endpoints will be treated as exploratory results.

The FAS will include the participants who are enrolled in the study and assigned to the study treatment. However, data on participants who violated the research protocol, such as enrolment without consent and registration outside the contract period, will be excluded. The PPS will include research participants who will be excluded from the FAS for the following reasons: violation of eligibility criteria, violation of exclusion criteria, violation of concomitant use of prohibited medications, and medication compliance rate > 120% or < 75%. The safety analysis set will include participants in whom research treatment has been initiated.

Summary statistics for the background data of study participants will be calculated for each group. Comparisons between groups will be made using the χ-square test or Fisher’s direct probability test for categorical variables and the two-sample t-test or Wilcoxon rank-sum test for continuous variables.

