#### Methods of analysis to handle protocol nonadherence and any statistical methods to handle missing data

Cases of violation of the concomitant use of prohibited medications will be included in the FAS but not in the PPS. Postprandial data of blood glucose, C-peptide, active glucagon-like peptide-1, and total bile acids are not included in the FAS and PPS because they are significantly less reliable. Missing data are treated as missing data and will not be complemented.

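### Observation ends with discontinuation, so patients discontinued before the single week-12 GSRS drop out of the FAS primary analysis, and the text conflicts on whether non-adherent and deviating patients are among them

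*Protocol article*

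**What the plan says.** In the Protocol article, the section on criteria for discontinuing or modifying interventions gives ten criteria for ending **observation**, not only treatment. They include HbA1c of 10% or more (criterion 2), stopping medication because disease or complications worsen (5), leaving the trial for illness or adverse events (6) and significant protocol deviation (9). The adherence criterion reads "8) significant nonadherence (< 75% of the number of tablets each participant plans to take internally or > 120"%). The same paragraph closes with a sentence that points the other way: "Even if there is a deviation from the research protocol, observations shall be continued as much as possible".

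Four further statements bear on the point:

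- Data management: "For the discontinued cases, data will be collected up to the point of discontinuation".
- The section on nonadherence and missing data: "Missing data are treated as missing data and will not be complemented".
- Outcomes sets a single follow-up value: "The primary endpoint of this trial will be the change in the total GSRS score from baseline to follow-up examination (12 ± 3 weeks after baseline".
- Statistical methods defines the FAS as those enrolled and assigned, less cases such as enrolment without consent. It lists compliance above 120% or below 75% among the PPS exclusions, and evaluates the primary endpoint by analysis of covariance.

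**The concern.** The FAS is meant to compare the groups as randomised. If a patient who stops treatment also stops being observed, and the only outcome is measured at the end, that patient is in the FAS by definition but contributes nothing to its primary result. The comparison is then limited to patients who reached the week-12 visit under observation.

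That is harmless if loss has nothing to do with outcome. It is not harmless if patients who do poorly leave more often in one group than in the other. The trial is open-label with an untreated control group, and one of the listed criteria is counted in tablets that only group A takes. A later analysis cannot repair this, because outcomes that were never collected cannot be recovered.

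**Working it through.** **Step 1. Does a discontinued patient have a primary outcome?** The criteria end observation, data collection stops at that point, the endpoint needs the value at 12 ± 3 weeks, and a missing value stays missing. A patient discontinued before the visit therefore has no change score and cannot enter the ANCOVA.

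**Step 2. Which patients does this reach?**

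| Reason | Groups it can affect | Is the text consistent? |
|---|---|---|
| HbA1c of 10% or more | both | yes: observation ends |
| Stopping medication for worsening; leaving for illness or adverse events | not limited to one group by the wording | yes: observation ends |
| Significant deviation | both | no: it ends observation, yet observation is to continue where possible |
| Tablet intake below 75% or above 120% | group A only | no: it ends observation, yet it also serves as a PPS exclusion |

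The PPS sentence is awkwardly worded, but the sensible reading is the FAS less the listed violations. The section on missing data supports this, because it keeps prohibited-medication violators in the FAS and out of the PPS. An adherence exclusion from the PPS is needed only if such patients are in the FAS with data.

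**Step 3. When can the adherence criterion act?** Under Plans for assessment and collection of outcomes, the logbooks and the week-12 survey forms are sealed and "sent to the data center in such a way that the investigators or researchers cannot confirm the contents of the responses". The threshold is a share of all planned tablets. It may therefore often be assessable only at the end, when the week-12 form already exists. The text does not say whether that form is then kept.

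**Step 4. Reproduce the plan's sample size.** Inputs from Sample size: difference 0.244, SD 0.412, alpha 0.05 (two-sided, from Statistical methods), power 0.80, ratio 1:1.

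n = 2 × [0.412 × (1.960 + 0.842) / 0.244]² = 44.76, so 45 per group. With 10% dropout, 45 / 0.90 = 50 per group. The stated figures reproduce. The allowance is the same in both groups; it restores precision and does nothing about bias.

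**Step 5. Illustrate the size.** The documents give no arm-specific loss rate, so the rates here are assumptions. Let a fraction m of group A be lost and none of group B. Let those observed in group A change by -0.441 and those lost by x. The control change is -0.197. The difference over all randomised patients is

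D = -0.197 - [(1 - m)(-0.441) + m·x]

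| m | x | Group A mean | D | 0.244/D - 1 |
|---|---|---|---|---|
| 0.10 | -0.197 (like controls) | -0.3969 - 0.0197 = -0.4166 | 0.220 | 11% |
| 0.10 | 0 (no change) | -0.3969 | 0.200 | 22% |
| 0.20 | -0.197 | -0.3528 - 0.0394 = -0.3922 | 0.195 | 25% |
| 0.20 | 0 | -0.3528 | 0.156 | 57% |

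**Step 6. What happens if there is no drug effect?** The rows with x = -0.197 measure dilution by patients who gain nothing from treatment. With no true effect they imply no bias, so they do not show a false-positive risk. That was simulated separately: 40,000 runs, 50 per group, SD 0.412, t-test, loss in group A only, and removal correlated with a poor change score.

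| Correlation | 10% removed: bias, type I error | 20% removed: bias, type I error |
|---|---|---|
| 0 | none, 5% | none, 5% |
| 0.3 | 0.024, 6% | 0.042, 8% |
| 0.5 | 0.039, 8% | 0.071, 13% |
| 1.0 | 0.078, 18% | 0.142, 43% |

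The bias favours BBG9-1 here because the set-up removes poor outcomes from that group. It is a consequence of the assumption and not evidence of direction.

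**The case against.** A reader might infer that non-adherent patients are simply taken out of the BBG9-1 group, so that the result is tilted in its favour. The documents do not support that, for four reasons.

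- The adherence criterion is the only clearly arm-specific one, and it may often act only once the week-12 form exists. Data up to the point of discontinuation would then include that form.
- The sentence on continued observation and the PPS definition suggest that non-adherent patients are meant to stay in the FAS. For them the defect is conflicting instructions, not demonstrated removal.
- The worsening in criterion 2 is glycaemic, not GSRS, and applies to both groups.
- Symptomatic patients in an untreated, open-label control group might also leave, which would push the estimate the other way.

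All of this stands. It is also true that data handling is deferred to a separate analysis plan and to blinded data review, so the absence of a missing-data sensitivity analysis is no finding. Moreover, ANCOVA on observed cases is valid if missingness depends only on group and the modelled covariates.

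None of this reaches patients discontinued before the visit for HbA1c, worsening, illness or adverse events. Whether their week-12 GSRS is collected is a rule of conduct, and the protocol says that it is not.

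**Conclusion.** The point holds in a limited form. As written, patients discontinued before the week-12 visit are lost to the primary analysis despite an FAS of all assigned participants. For non-adherent and deviating patients the sections contradict each other, and how many the adherence criterion would remove is uncertain.

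The primary comparison **can** be biased, if loss is related to outcome and differs between groups. The documents establish neither condition, nor a direction or size. The differences of 0.156 to 0.220 against 0.244 rest on assumed losses of 10% or 20% in group A alone; the plan's own 10% applies to both groups. The stated sample size is correct on its inputs, and this point by itself does not require changing it. The case for acting is that the correction is cheap and cannot be made after the outcomes have gone uncollected.

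**What to change.** 1. Leave the rules for stopping treatment as they are, and separate them from the end of observation.
2. Reconcile the discontinuation criteria, Data management and the analysis-set definitions, so that the adherence and deviation criteria define the PPS only.
3. Replace the Data management sentence with a statement that the week-12 GSRS form is collected from every randomised patient who has not withdrawn consent to data collection, whether or not treatment continued.
4. State that all such data are analysed as randomised in the FAS.
5. Optionally, add a sensitivity analysis for week-12 scores that are still missing, for example imputing missing group A patients from group B.

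The cost is some rewording and a few extra self-report forms. The expected effect may also be smaller, because patients who stopped treatment are counted. With all 50 per group followed, power is 84% at 0.244. Under the Step 5 assumptions it is 76% at 0.220, 68% at 0.200, 66% at 0.195 and 47% at 0.156.

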#### Confidentiality

Information that can identify research participants (e.g., name, address, and telephone number) will not be gathered or recorded in the CRF. Data management staff will use the central registration number when making inquiries to medical institutions.

#### Plans for collection, laboratory evaluation, and storage of biological specimens for genetic or molecular analysis for this trial/future use

Laboratory blood tests will be performed according to local clinical procedures, using standard and sterilized vacuum tubes for serum separation for C peptide, AST, ALT, gamma-glutamyltransferase, total cholesterol, high-density lipoprotein cholesterol, low-density lipoprotein cholesterol, triglyceride, blood urea nitrogen, creatinine, total bile acid, glycoalbumin; EDTA-2Na with NaF and fetal bovine serum for HbA1c; BD® P800 for glucagon-like peptide-1, glucose-dependent insulinotropic polypeptide, and glucagon. Furthermore, lipopolysaccharide-binding protein will be measured using enzyme-linked immunosorbent assay. Urinary laboratory tests will also be performed according to local clinical procedures. Gut microbiota will be measured using shotgun metagenomic sequencing. Metabolomes of serum, urine, and stool will also be measured using gas chromatography-tandem mass spectrometry.

### Statistical methods

#### Statistical methods for primary and secondary outcomes

Full analysis set (FAS) analysis will be performed for the primary and secondary endpoints. If necessary, per protocol set (PPS) analysis will be performed as a sensitivity analysis for the FAS analysis. In principle, the analysis should be performed at a two-sided significance level of 5%. The person responsible for the statistical analysis will prepare a separate statistical analysis plan that specifies the details of the statistical methods, including data handling. A statistical analysis plan will be prepared before the data are fixed. The primary endpoints will be treated as validation results, whereas the other endpoints will be treated as exploratory results.

The FAS will include the participants who are enrolled in the study and assigned to the study treatment. However, data on participants who violated the research protocol, such as enrolment without consent and registration outside the contract period, will be excluded. The PPS will include research participants who will be excluded from the FAS for the following reasons: violation of eligibility criteria, violation of exclusion criteria, violation of concomitant use of prohibited medications, and medication compliance rate > 120% or < 75%. The safety analysis set will include participants in whom research treatment has been initiated.

Summary statistics for the background data of study participants will be calculated for each group. Comparisons between groups will be made using the χ-square test or Fisher’s direct probability test for categorical variables and the two-sample t-test or Wilcoxon rank-sum test for continuous variables.

The primary endpoints will be evaluated using analysis of covariance. A two-sample t-test will be performed for between-group comparisons and a one-sample t-test will be performed for within-group comparisons. The secondary endpoints will be evaluated using a two-sample t-test or one-sample t-test. For data without a normal distribution, the log-transformation will be attempted; however, if it does not improve the distribution, Wilcoxon rank-sum test or Wilcoxon signed-rank will be performed. For the Bristol scale score, between-group comparisons will be performed using the Wilcoxon rank-sum test, and within-group comparisons will be performed using the Wilcoxon signed-rank test. For percentage endpoints, the χ-square test or Fisher’s direct probability test will be performed. For safety, a list of all adverse events will be prepared for each group in the safety analysis population; if necessary, comparisons between groups will be made using Fisher’s direct probability test.

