#### Composition of the data monitoring committee, its role, and reporting structure

The data monitoring committee consists of research investigators and statistical analysts. The handling of data deviating from the study design and the handling of missing data will be evaluated in a blinded manner prior to analysis to determine the handling of all data.

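### The per-protocol set is worded as the violators removed from the full analysis set, which contradicts its sensitivity role and the protocol's own rule on prohibited medication

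*Protocol article*

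**What the plan says.** All references are to the protocol article.

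- **Role of the sets** (Statistical methods for primary and secondary outcomes): "Full analysis set (FAS) analysis will be performed for the primary and secondary endpoints". If needed, "per protocol set (PPS) analysis will be performed as a sensitivity analysis for the FAS analysis".
- **FAS** (same section): "The FAS will include the participants who are enrolled in the study and assigned to the study treatment". An exception follows: "data on participants who violated the research protocol, such as enrolment without consent and registration outside the contract period, will be excluded".
- **PPS** (same section): "The PPS will include research participants who will be excluded from the FAS for the following reasons". The reasons are "violation of eligibility criteria, violation of exclusion criteria, violation of concomitant use of prohibited medications, and medication compliance rate > 120% or < 75" percent.
- **Nonadherence** (the later section on methods for protocol nonadherence and missing data) gives a rule for one of these reasons: "Cases of violation of the concomitant use of prohibited medications will be included in the FAS but not in the PPS".
- **Setting:** the trial is open-label (Trial design), and the control group receives no medication (Explanation for the choice of comparators).
- **Deferral:** a separate statistical analysis plan, to be written before the data are fixed, will give details including data handling.

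**The concern.** A per-protocol set is normally the full analysis set with the violators taken out. Here the sentence runs the other way: the violators are what the PPS contains, and they are said to have been taken out of the FAS. An analyst who followed it would get both sets wrong. The primary analysis would lose randomised participants because of how they behaved or were treated after allocation, and the sensitivity analysis would be run on those same people.

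The FAS is the set to protect in an open-label trial, because it carries the primary comparison. One of the four listed reasons, tablet compliance, can arise in one arm only. A published protocol is also the record against which the reported FAS will be checked, and this text would support two different analysis sets.

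**Working it through.** **Step 1. The PPS sentence against the PPS's role.** Let V be the participants with any of the four listed violations. Literally, PPS = V and V lies outside the FAS, so the two sets share nobody. An analysis on a disjoint set of people cannot test the sensitivity of the FAS result.

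**Step 2. The two sections side by side, reason by reason.**

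| Reason | PPS sentence, read literally | Nonadherence section |
|---|---|---|
| Eligibility criteria violated | out of FAS, in PPS | silent |
| Exclusion criteria violated | out of FAS, in PPS | silent |
| Prohibited concomitant medication | out of FAS, in PPS | in FAS, out of PPS |
| Compliance above 120% or below 75% | out of FAS, in PPS | silent |

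The contradiction is direct for one reason. For the other three, no other text states membership.

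**Step 3. Does the FAS definition settle the other three?** It starts from everyone enrolled and assigned, which would keep them in. It then excludes protocol violators, giving two cases introduced by *such as*. Both are failures of valid enrolment, which suggests a narrow intention, but the list is not closed. The four PPS reasons are themselves departures from the protocol, so a reader can bring them under it.

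**Step 4. Compliance.** Only group A takes tablets, so a compliance rule can remove only group A participants. If a fraction p of group A is removed, the group A mean shifts by

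p × (mean change of those retained − mean change of those removed).

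The document gives neither p nor the difference in means. The rule also covers over-compliance, where even the sign is unclear. No bias figure follows.

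**Step 5. The plan's own figure** (Sample size: difference 0.244, SD 0.412, alpha 0.05, power 0.80, ratio 1:1).

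n per group = 2 × (1.96 + 0.8416)² × (0.412 / 0.244)² = 2 × 7.849 × 2.851 = 44.8, rounded up to 45.

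With 10% dropout: 45 / 0.9 = 50. Both stated figures reproduce (the t-test version gives 45.7, so 46). Neither depends on the PPS wording.

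**Step 6. Illustration of numbers lost.** The violation rate v is not given, so 5% to 30% is **assumed**, equal in both arms and with effect and SD unchanged. Power = Φ(0.244 / (0.412 × √(2/n)) − 1.96). At n = 45 this is Φ(2.809 − 1.96) = 80.2%.

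| v (assumed) | FAS without violators, n per group = 45(1 − v) | Power | Literal PPS, n per group = 45v | Power |
|---|---|---|---|---|
| 5% | 42.75 | 78.2% | 2.25 | 9.1% |
| 10% | 40.5 | 76.0% | 4.5 | 14.2% |
| 20% | 36 | 71.0% | 9 | 24.1% |
| 30% | 31.5 | 65.2% | 13.5 | 33.7% |

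This shows lost precision only. It says nothing about bias.

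**The case against.** The strongest reply is that the meaning is recoverable. The PPS is called a sensitivity analysis for the FAS, and prohibited-medication cases are placed in the FAS and out of the PPS. Only one definition fits both: the FAS minus the listed violators. The sentence is then a drafting or translation slip, and nobody would really run a PPS on violators. This stands as an account of intent. It does not make the sentence correct, and it settles three of the four reasons only by inference.

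A second reply is that data handling is left to the analysis plan, which may hold a closed list of FAS exclusions. That is fair as regards the open wording alone, which would be a minor point. It does not cover a definition that the protocol states wrongly and contradicts elsewhere.

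Three stronger readings are tempting and are not supported:

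- **That the FAS sentence itself drops non-compliers.** It does not mention compliance. Only the PPS sentence, or a broad reading of the FAS exception, links compliance to FAS exclusion.
- **That the bias toward BBG9-1 can be sized.** That needs a non-compliance rate and a link between non-compliance and response. The document gives neither; its only 10% is the dropout rate.
- **That investigators could choose FAS membership knowing the arm.** The protocol does say "The data monitoring committee consists of research investigators and statistical analysts". But data handling is to be blinded, and Plans for assessment and collection of outcomes has the logbooks (including adherence) and the 12-week survey forms sealed and sent to the data center unseen by investigators. Nothing says that adherence is shown unmasked to the committee or that it has discretion over FAS membership.

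**Conclusion.** The PPS sentence is wrong as written and should be corrected before the data are fixed. Two things are established from the text alone: it is incompatible with the PPS's stated role, and it directly contradicts the nonadherence section for prohibited medication. For eligibility, exclusion-criteria and compliance violations the finding is weaker: the wrong text is left uncorrected, and the FAS exception is loose enough to be read in its support.

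The consequence is conditional. If compliance were applied to the FAS, post-randomisation exclusions could occur in group A only. The amount and direction of bias are unknown. The power losses shown above rest on assumed violation rates and illustrate only what literal use would cost in numbers. The stated sample size does not change. Nothing shows that the trial team intends the literal reading.

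**What to change.** Replace the two definitions with:

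> FAS: all randomised participants analysed as assigned, excluding only those enrolled without consent or registered outside the contract period.
>
> PPS: the FAS minus participants with a violation of inclusion or exclusion criteria, use of prohibited concomitant medication, or (group A) compliance below 75% or above 120%. These participants remain in the FAS.

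Delete *such as* from the FAS exception so that the list is closed, and carry the same text into the analysis plan. The definitions use the protocol's own criteria and agree with the nonadherence section, so that section needs no change.

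The cost is wording only: no change to sample size, data collection or the planned tests.

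One limit remains. FAS membership does not ensure a week-12 score. The same compliance limits appear among the criteria for discontinuing observation (alongside a statement that observation continues as far as possible after deviations), data for discontinued cases are collected only up to that point, and missing values are not filled in. The new wording fixes who belongs to each set, not whether their outcome is observed.
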